## Abstract

**Background:**

The importance of family support in addressing maternal anxiety and depression during pregnancy is widely recognized. However, cultural nuances and healthcare system dynamics in China call for tailored interventions for perinatal mental health. Family-based companion video sharing via mobile health (mHealth) emerges as a potentially effective and scalable approach, delivering cost-effective emotional support and information dissemination. It is imperative to conduct rigorous evaluations through randomized controlled trials to assess its impact on maternal mental health. This study aims to evaluate the efficacy of family support-based mobile companion video sharing, providing data support for advancing perinatal mental health interventions in China.

**Methods:**

The study involves 40 pregnant women with mild to moderate depression symptoms and conducts an eight-month randomized controlled trial. Participants are randomly assigned to the intervention or control group. The intervention group receives a mHealth intervention involving six weeks of themed video sharing with their caregivers, based on mindfulness theory. Participants are required to record and share videos with their caregivers via WeChat according to weekly themes, in collaboration with the research team. The research team also regularly sends healthcare messages, creating a bidirectional intervention. The control group only receives healthcare messages. All participants are required to complete five follow-up visits, with depression levels assessed using the 5-item short form of the EPDS (EPDS-Dep-5).

**Discussion:**

This study innovatively explores mHealth interventions, specifically family-based companion video sharing to improve maternal mental health during pregnancy. In contrast to traditional interventions, this study emphasizes two-way communication between the mother and her companion, facilitating mutual support. If successful, this approach could inform perinatal mental health interventions globally.

**Trial registration:**

This study registered at ClinicalTrials.gov (ChiCTR2400084685) on May 22, 2024.

## Background

1

The shift from the traditional biomedical model to the biopsychosocial framework has increased focus on mental health issues (1). The implementation of China’s two-child and three-child policies, leading to more pregnant women, has drawn attention to the mental health of perinatal women (2). Perinatal depression (PND), characterized by symptoms such as despondency and anxiety during pregnancy, childbirth, or after abortion, is a common complication in both gestational and postpartum periods (3, 4). Factors such as social support, occupational factors, healthcare access, and fluctuations in maternal hormone levels can predispose pregnant women to anxiety and depression (5–7). PND exerts deleterious effects not only on the mother and her immediate family but also has negative impacts on the physical and psychological well-being of the child, leading to outcomes like preterm labor, mother-infant bonding, and low birth weight (8–11). The prevalence of antenatal depression ranges from 15.0% to 25.0%, while postnatal depression incidence varies between 7.0% and 30.0%. In China, the overall prevalence of perinatal depression is estimated at approximately 16.3% (12, 13). A discernible correlation exists between the prevalence of PND and a nation’s level of development, with higher-income countries exhibiting lower prevalence rates compared to middle- and low-income counterparts (14). The prevalence of maternal depression varies across different life stages, with the cumulative prevalence rates for perinatal depression, antenatal depression, and postpartum depression averaging at 26.3%, 28.5%, and 27.6%, respectively (15). A study conducted in the United States revealed that nearly 50% of perinatal pregnant women displaying major depressive symptoms did not initiate timely treatment, with over 75% failing to adhere to treatment regimens (16). During the COVID-19 pandemic, the prevalence of prenatal depression in China surged to 71.0%, while in Poland, the prevalence of postpartum depression approached 74.0% (17). In recent years, effective prevention and management strategies for PND have emerged as crucial challenges receiving attention from scholars worldwide.

Medication-based treatments for depression have detrimental effects on both maternal and offspring health. Therefore, targeting psychosocial factors in perinatal depression (PND) shows promise as an effective strategy. Traditional interventions, including nursing protocols, health promotion, and psychological therapies such as interpersonal psychotherapy (IPT) and relaxation techniques, aim to alleviate perinatal anxiety and depression (18–22). These interventions often last weeks to months and face challenges with patient adherence, which can limit their effectiveness in reducing PND. Thus, it is urgently necessary to explore novel approaches to improve treatment outcomes (23).

Mobile Health (mHealth) has garnered attention as a promising avenue, with the World Health Organization (WHO) actively promotes adopting digital technologies to improve various patient care models (24–28). mHealth apps play a pivotal role in patient education, disease self-management, remote patient monitoring, and overall improvement of quality of life (29–31). For instance, the Interactive Maternal Information and Emotional Support Group (IMAGINE) demonstrated improved emotional management and acceptance of mental health care. This was achieved through personalized communication with guidance specialists and peer support (32). Similarly, a Japanese mHealth-based randomized controlled trial (RCT) showcased the preventive impact of a mobile health counseling app on postpartum depressive symptoms (33). Studies on Positive Thinking-Based Interventions (MBIs) have highlighted the efficacy of digitally guided self-help interventions in alleviating maternal depression throughout the perinatal period, with mHealth-based interventions exhibiting lower dropout rates and greater acceptability compared to face-to-face interventions (34–36). These interventions use various mHealth platforms to deliver support, such as online support groups, email or text messaging, mobile apps, and web pages (32, 33, 37–40). Despite the widespread use of mHealth, its effectiveness in reducing perinatal depression or anxiety remains inconclusive, with only a few apps being considered high quality (41, 42). Therefore, there is a critical need for the development of high-quality mHealth apps and rigorous evaluation of their potential to improve perinatal maternal mental health. This field warrants further research and investment to provide effective and accessible support for pregnant women experiencing depression and anxiety.

Studies have underscored the significant role of emotional, material, and informational support from family members in reducing maternal anxiety and depression, thus promoting healthy mental well-being during pregnancy (43, 44). Moreover, community-based comprehensive family interventions, involving family members in the care of pregnant women with postpartum depression, have shown promise in alleviating depressive symptoms and improving overall mental health outcomes (45). Notably, Liu’s study emphasizes that engaging caregivers in the care process not only helps dispel misconceptions about depression but also enhances their understanding of proper daily care practices (46). In many countries, maternal support during pregnancy primarily involves hospitals and communities in tandem with routine care. However, in Chinese cities, it often relies heavily on hospital support alongside family involvement. Due to these cultural and healthcare differences, the impact of home-based maternal support on perinatal depression deserves special attention in China. One promising intervention is family-based companion video sharing, which can serve as an accessible mHealth strategy. Through sharing videos documenting the caregiving process, the mother’s daily experiences, and insights, emotional support and essential information can be swiftly delivered, meeting the mother’s care needs effectively. This intervention aligns with preferences for easily implementable and cost-effective solutions while addressing societal needs. Consequently, an urgent need exists for a randomized controlled trial (RCT) to evaluate the feasibility and long-term behavioral effects (The situation of depressive symptoms in pregnant women 4 weeks after delivery) of family support-based video sharing. This trial should particularly focus on improving perinatal maternal mental health among pregnant women in China. Such research would shed light on the efficacy and practicality of this intervention within the Chinese healthcare landscape.

According to the Individual and Family Self-Management Theory (IFSMT) (47), self-management is viewed as a relatively complex process, and the theory consists of three dimensions: content, process, and outcome. The theory emphasizes improving individual and family self-management processes to achieve positive results, including behavioral changes, use of health and wellness services (proximal outcomes), and health status, quality of life, and healthcare expenditures (distal outcomes). Therefore, the family support-based companion video focuses on the pregnant woman and her family members to address perinatal maternal depression. By capturing perspectives from both the pregnant woman and her companion, the intervention aims to improve maternal depression and related health indicators. In addition, the content of the intervention shared in the companion video draws from Mindfulness-Based Interventions (MBIs), a form of psychotherapy that redirects attention to present moment experiences (48). Based on mindfulness theory, different themes guide pregnant women to objectively view the changes in their physical, psychological, and social environments during pregnancy and childbirth. While MBIs have demonstrated benefits for pregnant women internationally, these interventions are still at an early stage of development in China (49, 50).

This study designs a randomized controlled trial to evaluate the intervention effect of family support-based mobile companion video sharing on the mental health of perinatal women. Compared to previous mobile health intervention studies that used text or images as the intervention medium, this study has two innovative points: 1) The intervention medium is WeChat video, and the intervention mode is a bidirectional interaction between researchers and participants; 2) The intervention emphasizes the active participation of participants’ family members. This innovative intervention approach is expected to provide new perspectives and effective means for perinatal mental health management.

## Methods

2

### Objectives

2.1

This study aims to evaluate how effective a mobile health intervention using family support-based companion video sharing is in reducing perinatal maternal depressive symptoms. Additionally, the study also aims to evaluate the acceptability and feasibility of companion video sharing among pregnant women and their family members, and to explore factors influencing to this intervention.

### Trial design

2.2

This study adopts a randomized controlled trial design and is conducted at Dongying People’s Hospital, Shandong Province, China. The intervention involves family support-based companion video sharing among perinatal women and their families. Forty participants are randomized into two groups: a 20-participant intervention group receiving companion video sharing and a 20-participant control group receiving traditional care. The research flowchart is shown in **Figure 1**.

**Figure 1 f1:**
[figure not shown]
Study flowchart.

### Recruitment

2.3

We began recruiting perinatal pregnant women on August 12, 2024 using a multi-channel approach. This approach encompassed online platforms, hospital settings, and community outreach. Initially, announcements related to the trial were shared through the WeChat public account of Dongying People’s Hospital and its affiliated medical institutions, providing links to an electronic questionnaire for interested perinatal mothers and their companions to submit their contact information. Additionally, medical staff at the Obstetrics and Gynecology Specialist Outpatient Clinic of Dongying People’s Hospital inform perinatal pregnant women attending appointments about the study and provide questionnaires to those interested or showing signs of depression. Moreover, community health workers at various health service centers in urban areas associated with Dongying People’s Hospital promote the study and enroll eligible participants by administering questionnaires.

After identifying interested individuals who met the inclusion criteria, researchers clarified the study’s objectives and procedures. Then, the study’s medical personnel meticulously screened and selected eligible perinatal women based on predefined criteria. Each participant received a detailed letter of informed consent (refer to Appendix), detailing the study’s aims, procedures, and potential implications. After both parties mutually agreed and signed the informed consent, the participants who completed this process formed the recruited cohort. Random allocation then determined the assignment of participants to either the intervention group (companion video-sharing group) or the control group (traditional care group).

### Eligibility criteria

2.4

#### Inclusion criteria

2.4.1

(1) gestational age of 12 weeks (within a one-week window); (2) age of 18 years or older; (3) absence of plans for pregnancy termination; (4) commitment to reside in Shandong for at least one year and availability for study follow-up (with all visits conducted at Dongying People’s Hospital until delivery); (5) EPDS-Dep-5 score of ≥ 4 during depression screening (51); (6) consistent presence of a designated companion throughout pregnancy; and (7) comprehensive understanding and voluntary participation in the trial by both pregnant women and their companions (informed consent).

#### Exclusion criteria

2.4.2

Exclusion criteria include: (1) lacking a smartphone or being unfamiliar with WeChat; (2) receiving ongoing psychiatric treatment or using psychotropic medications; (3) having significant organ dysfunction that impairs daily functioning; (4) participating concurrently in a similar depressive intervention clinical study; and (5) refusing to participate in the study.

### Sample size

2.5

This study is a randomized controlled trial with an intervention group using companion video sharing and a control group receiving usual care. The primary outcome indicator observed is the EPDS score of the study population. Based on a previous intervention study (52), the EPDS score of the intervention group was 12.0 at 36 weeks’ gestation, while the control group had a score of 14.9 at the same gestational age. We set the hypothesis certainty (1-β) at 90%, and the significance level (α) at 0.05. Using PASS 15.0, the calculated sample size for the study was 32 participants, with 16 in the companion video sharing group and 16 in the traditional care group. Considering a 20% attrition rate, 40 participants were included in the study.

Group sample sizes of 20 and 20 achieve 99.472% power to reject the null hypothesis of equal means when the population mean difference is μ1 - μ2 = 12.0 - 14.9 = -2.9 with standard deviations of 2.4 for group 1 and 1.4 for group 2, and with a significance level (alpha) of 0.050 using a two-sided two-sample unequal-variance t-test.

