#### Primary outcome

2.10.1

The severity of maternal anxiety and depression is primarily assessed by the Edinburgh Postnatal Depression Scale (EPDS), the scale was developed by Cox et al. (53) in 1987 and introduced in 1998. The revised EPDS consists of 10 items, each divided into 4 levels: “Never,” “Occasionally,” “Often,” and “Always,” corresponding to scores of 0, 1, 2, and 3, respectively, with items 1, 2 and 4 being reverse scored. The total score ranges from 0 to 30. The Cronbach’s alpha coefficient of this scale is 0.87, indicating high validity and reliability (54). The Chinese EPDS-Dep-5 scale used in this study consists of items 1, 2, 8, 9, and 10 from the EPDS scale, and the cutoff score for the EPDS-Dep-5 scale is 4 points, meaning that when the total score of the assessment is ≥4 points, it indicates that the pregnant woman is at high risk for depression. Although the full version of the EPDS is more commonly used, this study chose the EPDS-Dep-5 mainly based on the following considerations: (1) This 5-item short version, which has been shown to be highly correlated with the full version (r≈0.90), does a good job of distinguishing depression in terms of sensitivity and specificity; (2) The sample size of this study is relatively small, and repeated assessments during the intervention process require a shorter version to reduce participant burden and reduce the chances of losing participants; (3) The short version can be completed in just 0.5–1 minute, making it better for new moms in the early days when they might not have much energy.

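### The sample size and power in section 2.5 are not derived for the EPDS-Dep-5, the only depression scale the trial collects, so the stated 90% and 99.472% are unsupported

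*Protocol article*

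**What the plan says.** Section 2.5 (Sample size) identifies the outcome in these words: "The primary outcome indicator observed is the EPDS score of the study population". The planning values come from an earlier intervention study: "the EPDS score of the intervention group was 12.0 at 36 weeks’ gestation, while the control group had a score of 14.9". The power statement then uses "the population mean difference is μ1 - μ2 = 12.0 - 14.9 = -2.9", with "standard deviations of 2.4 for group 1 and 1.4 for group 2", and sets "the significance level (α) at 0.05" for a two-sided unequal-variance t-test. From this the section reports 16 per arm for 90% power, 40 women after allowing for 20% attrition, and 99.472% power with 20 per arm.

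Section 2.10.1 (Primary outcome) opens with the EPDS, described as ten items scored 0 to 3 with a total of 0 to 30. It then says: "The Chinese EPDS-Dep-5 scale used in this study consists of items 1, 2, 8, 9, and 10 from the EPDS scale". The Methods paragraph of the abstract agrees, describing follow-up visits "with depression levels assessed using the 5-item short form of the EPDS (EPDS-Dep-5". Entry under section 2.4.1 requires an EPDS-Dep-5 score of at least 4. Table 2 lists EPDS-Dep-5 at recruitment and at T1 to T5 and has no row for the ten-item scale.

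**The concern.** The quantity powered in section 2.5 and the quantity measured in the rest of the protocol are different scores. A difference of 2.9 points and SDs of 2.4 and 1.4 taken from one scale do not carry over unchanged to a sub-scale with half the range. The protocol gives neither a difference nor an SD for the EPDS-Dep-5, and no conversion.

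Section 2.5 is the only quantitative justification for enrolling 40 women. If it stays as written, a reader of a null result would judge it against 90% or 99% power that was never worked out for the outcome analysed.

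**Working it through.** **Inputs.** From section 2.5: means 12.0 and 14.9, SDs 2.4 and 1.4, two-sided α = 0.05, Welch t-test, 16 analysed and 20 enrolled per arm. From section 2.10.1: item scores 0 to 3, full scale 0 to 30, five items in the EPDS-Dep-5, correlation between the forms about 0.90.

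**1. Reproduce the stated power.** The noncentrality is 2.9 / √(2.4²/20 + 1.4²/20) = 2.9 / 0.621 = 4.67, with Satterthwaite df 30.6. Noncentral-t power is 99.472%, exactly as stated. The same inputs with 16 per arm give 97.95%. (That this exceeds the 90% target is a separate matter. Sixteen per arm is recovered if both SDs are 2.4, where 15 gives 89.1% and 16 gives 91.1%.) The attrition step, 32 / (1 − 0.20) = 40, is correct.

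**2. Can the inputs be EPDS-Dep-5 values?** The protocol does not print the range of the short form. It follows from the scoring: 5 × 3 = 15. For any score confined to 0–15 with mean m, the variance is at most m(15 − m). At m = 14.9 this is 14.9 × 0.1 = 1.49, so the SD is at most √1.49 = 1.22, below the 1.4 used. If 14.9 is a rounded 14.85, the bound rises to √(14.85 × 0.15) = 1.49, but an SD at that bound would need 99% of women at 15 and 1% at 0. The inputs as stated are therefore not short-form values. They fit the 0–30 scale that section 2.10.1 calls the EPDS.

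**3. Does r ≈ 0.90 bridge the two scales?** Not by itself, because a correlation supplies neither a mean difference nor an SD. It can be used only with added assumptions. Suppose the two five-item halves have equal variance and each carries half the difference. Then r = √((1 + ρ)/2) = 0.90 gives a between-half correlation ρ = 2 × 0.81 − 1 = 0.62. The SD ratio is 1/√(2 × 1.62) = 0.556, and the standardised effect is multiplied by 0.5/0.556 = 0.9.

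**4. Power on the EPDS-Dep-5 under stated assumptions.** Same Welch formula, 16 analysed per arm. No row is a protocol figure.

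| Assumed difference | Assumed SDs | Power |
|---|---|---|
| 1.45 (halved) | 1.2 and 0.7 (halved) | 98% |
| standardised effect × 0.9 (step 3) | – | 95% |
| 1.45 | 2.4 and 1.4, each × 0.62 | 90% |
| 1.45 | 2.4 and 1.4 unchanged | 52% |

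**5. Detectable difference.** With 16 per arm, a common SD and 90% power, the detectable difference is about 1.18 SD. For illustration, that is 1.18, 1.78 or 2.37 points at an SD of 1.0, 1.5 or 2.0.

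**The case against.** The strongest reply is that the change of scale may cost little. A five-item sub-total normally varies less than the ten-item total, so the SD shrinks along with the difference. Under the equal-halves assumption, a correlation of 0.90 leaves about 95% power with 16 per arm. This stands. It shows that the change of scale alone need not take power below 90%.

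A reader might infer the opposite, that the trial is underpowered. The documents do not support that. Pairing a difference of 1.45 with a common SD of 2.0, 2.5 or 3.0 gives 51%, 36% or 26% power. Those SDs, however, exceed the root-mean-square planning SD of the full scale, √((2.4² + 1.4²)/2) = 1.965. Such rows require the planning SDs themselves to be too small for this population, and no document shows that. Nor must the SDs halve for the 90% claim to survive: with a difference of 1.45, a common SD of about 1.22 is enough. The 52% row is likewise an outer case, because it gives the short form the full scale's spread.

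Two further replies carry some weight. Section 2.10.1, the abstract and Table 2 leave little doubt about which instrument is used. The Discussion also lists the small sample as a limitation and speaks of preliminary evidence. Neither repairs the power statement. Reading EPDS in section 2.5 as shorthand for the short form fails on step 2.

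**Conclusion.** The power statement is wrong as written. The 99.472% is correct arithmetic for a score the trial does not collect, and neither it nor the 90% is derived for the EPDS-Dep-5. The supportable conclusion is that power for the measured primary outcome is unknown from this document, not that it is low. The illustrative values run from 52% to 98% at 16 analysed per arm, and the scenarios that scale difference and SD consistently give 95% to 98%. The conclusion rests on the short form being scored 0 to 3 per item, as section 2.10.1 describes for the EPDS. Section 2.5 does not say in words which form the earlier study used; the ten-item form is inferred from the name and from the SD bound.

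**What to change.** - Name EPDS-Dep-5 as the primary outcome in section 2.5 and in the opening sentence of section 2.10.1.
- Replace both power figures with power over a stated range of EPDS-Dep-5 differences and SDs at 16 analysed per arm, with each assumption labelled.
- State the difference detectable with 90% power, about 1.18 SD, in EPDS-Dep-5 points across that SD range.
- Pooled, blinded baseline EPDS-Dep-5 data, where available, may inform the SD range, but only with a caveat. The entry rule of at least 4 truncates those scores, so their SD may understate the spread at 36 weeks and flatter the power.
- Keep n = 40, the instrument and the visit schedule.

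The cost is one recalculation and some rewording, and the stated power may become less favourable. No extra participants or visits are needed.

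### The 16 per group stated for 90% power does not follow from the SDs and test that the protocol prints, which give 11 per group

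*Protocol article*

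**What the plan says.** Everything relevant is in the protocol article, section 2.5 (Sample size).

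- **First paragraph.** It takes 36-week EPDS means from an earlier trial ("the EPDS score of the intervention group was 12.0", against 14.9 in controls). It sets the power target ("We set the hypothesis certainty (1-β) at 90" per cent) and alpha at 0.05. It then reports the PASS 15.0 result: "the calculated sample size for the study was 32 participants, with 16 in the companion video sharing group". No SD and no test are named for that result. The total is raised for dropout: "Considering a 20% attrition rate, 40 participants were included in the study".
- **Second paragraph.** It states that "Group sample sizes of 20 and 20 achieve 99.472% power to reject the null hypothesis of equal means" for a mean difference of -2.9. The spread it assumes is "standard deviations of 2.4 for group 1 and 1.4 for group 2". The same sentence repeats alpha 0.05 and names the method as "using a two-sided two-sample unequal-variance t-test".

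The SDs and the test in the second paragraph are the only ones given for either calculation.

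**The concern.** The two paragraphs share the means and alpha and justify the same 40 women, so a reader will take the SDs and test of the second as the basis of the first. On that basis 16 per group is well above what 90% power needs. Either the 16 rests on an input that is not printed, or it is wrong.

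At stake is whether the justification can be reproduced. If the 16 was computed with larger SDs than those printed, then 99.472% is not the power on the basis that fixed the sample size. The power at 16 per group could be about 91% or about 98%, depending on which inputs were used, and a reader cannot tell which. In addition, the only power figure quoted is for the enrolled 20 per group, although the paragraph before it expects to lose 20%.

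**Working it through.** **Inputs** (all from section 2.5, except the 1:1 allocation, which is in section 2.6): difference d = 14.9 - 12.0 = 2.9; SDs 2.4 and 1.4; two-sided alpha 0.05; unequal-variance t-test; equal groups of size n; target power 90%; attrition 20%.

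**Formulas.**
- Variance of the difference: v = (2.4² + 1.4²)/n = (5.76 + 1.96)/n = 7.72/n.
- Noncentrality: λ = 2.9/√v.
- Satterthwaite degrees of freedom with equal n: df = (n - 1) × 7.72²/(5.76² + 1.96²) = 1.610 × (n - 1).
- Power = P(|T| > t(0.975, df)), with T noncentral t on df degrees of freedom and noncentrality λ.

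**Step 1: reproduce the protocol's power figure.** For n = 20: v = 0.386, √v = 0.6213, λ = 4.668, df = 30.59, critical t = 2.041. Power = 99.472%, the printed figure to every decimal. The method is therefore the one behind the second paragraph.

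**Step 2: find the n for 90% power from the same inputs.**

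| n per group | √v | λ | df | critical t | power |
|---|---|---|---|---|---|
| 10 | 0.8786 | 3.301 | 14.49 | 2.138 | 86.8% |
| 11 | 0.8377 | 3.462 | 16.10 | 2.119 | 90.1% |
| 16 | 0.6946 | 4.175 | 24.15 | 2.063 | 97.95% |
| 20 | 0.6213 | 4.668 | 30.59 | 2.041 | 99.472% |

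The smallest n reaching 90% is 11 per group, 22 in total, against the stated 16 and 32. Simulation with 100,000 trials per n gives 86.7%, 89.95%, 97.96% and 99.45% at 10, 11, 16 and 20. So 11 sits on the 90% line; 12 per group gives 92.7% by the formula. Neither is near 16.

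**Step 3: try other readings of the same SDs.** An equal-variance t-test with pooled SD √((5.76 + 1.96)/2) = 1.965 needs 11 per group, and the normal approximation needs 10. The average SD of 1.9 gives the same 11 and 10. None gives 16.

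**Step 4: look for inputs that do give 16.** Two sets do, and neither is what the section prints:
- Common SD of 2.4 in both groups: v = 2 × 5.76/16 = 0.72, λ = 2.9/0.8485 = 3.418, df = 30, power 91.1%. At 15 per group it is 89.1%, so 16 is the minimum. At 20 per group it is 96.1%.
- SDs 2.4 and 1.4 with alpha 0.01: power 90.4% at 16 and 87.8% at 15.

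**Step 5: attrition.** 32/0.8 = 40, as stated. From 22, 22/0.8 = 27.5, so 28 enrolled (14 per group). With 40 enrolled and 20% lost, 20 × 0.8 = 16 per group remain. Power at 16 under SDs 2.4 and 1.4 is 97.95%, which is 99.47 - 97.95 = 1.52 points below the quoted figure.

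**The case against.** Four points can be made for the protocol.

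1. **The mismatch is conservative.** Under the printed SDs the trial is larger than it needs to be and keeps 97.95% power after the planned loss, against a target of 90%. This stands. No change in sample size follows, and a reader who inferred from the faulty figure that the trial has low power would be wrong on these inputs.
2. **The 16 may be a deliberate cautious choice.** A reader might infer that the first paragraph used an SD of 2.4 in both groups, and that the authors then moved to a smaller control-group SD to show a better power. The documents do not support that. No SD is printed for the 16, and alpha 0.01 with the printed SDs also yields it. Each explanation contradicts something the section states (the control-group SD in one case, alpha in the other). What can be shown is only that 16 does not follow from the printed inputs.
3. **The 99.472% is not an error.** A reader might also infer that it overlooks the plan's own attrition. But the sentence gives its condition openly, 20 and 20, and is correct for that condition; the dropout allowance is applied properly one sentence earlier. The gap to the figure at 16 per group is about 1.5 points. What remains is that the power at the number expected to be analysed is the more useful one to quote.
4. **An article condenses.** That would excuse a missing detail. It does not excuse two printed figures that conflict.

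**Conclusion.** The 16 per group (32 in total) for 90% power is wrong as stated: the printed difference, SDs, test and alpha give 11 per group (22 in total; 28 enrolled after 20% attrition). The stated total exceeds the reproduced one by 10 women, or 10/22 = 45%. At 16 per group the printed inputs give 97.95%, so the 16 and the 99.472% cannot share one set of inputs.

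This calls for correcting stated figures. It is not evidence of low power, and 40 women can stand. The conclusion takes the means and SDs as given, on the full EPDS. Whether they suit the EPDS-Dep-5 that the trial administers is a separate question and adds nothing to this point.

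**What to change.** Keep 40 women and rewrite section 2.5 on one basis.

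- Check the PASS output and state the SDs, test and alpha actually used for the 16 per group.
- If the SDs were 2.4 and 1.4, correct the requirement to 11 per group, and state that 16 evaluable per group after 20% attrition gives about 98% power.
- If a larger SD was used, state it and quote power on that same basis. For example, a common SD of 2.4 would give 16 per group and about 91% power. This value should not be written in unless the output shows it.
- In either case, report power at the 16 per group expected after attrition. If 99.472% is kept, label it as the figure for 20 per group with no attrition under SDs 2.4 and 1.4.

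The cost is one look at stored output and one rewritten paragraph. Recruitment and analysis do not change.
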